# Clinical and Patient-Reported Outcomes Following Multidisciplinary Management of Cancer-Related Pain: Protocol for a Prospective Observational Pre-Post Study

**DOI:** 10.2196/92566

**Published:** 2026-08-27

**Keywords:** pain, cancer, multidisciplinary, patient, committees, clinical

## Abstract

**Background:**

Cancer-related pain remains highly prevalent and frequently undertreated despite advances in oncological therapies and analgesic strategies. Multidisciplinary approaches are recommended to optimize complex cancer pain management and integrate supportive care; however, robust real-world evidence evaluating their measurable clinical and patient-reported impact remains limited. Structured multidisciplinary cancer pain committees may be associated with changes in pain outcomes, quality of life, and patient experience, but prospective evaluations in routine clinical practice are scarce.

**Objective:**

The primary objective of this study is to describe changes in pain intensity following multidisciplinary evaluation in patients with cancer-related pain. Secondary objectives include describing changes in quality of life, pain interference, opioid consumption, treatment-related adverse effects, and patient-reported experience measures (PREMs) following multidisciplinary cancer pain committee assessment.

**Methods:**

This is a prospective, single-center, longitudinal, observational pre-post study conducted in a tertiary university hospital. A total of 68 adult patients with cancer-related pain referred to a multidisciplinary cancer pain management committee will be consecutively included in the study. Clinical variables and patient-reported outcomes will be collected at baseline (T0, before committee evaluation) and at 60 days following multidisciplinary committee assessment (T1). The primary outcome measure will be the change in pain intensity measured using the visual analog scale. Secondary outcomes include pain interference assessed with the Brief Pain Inventory–Short Form; health-related quality of life measured with the EQ-5D; and opioid consumption, treatment-related adverse effects, and PREMs, including patient satisfaction, assessed using the Likert scale. Pre-post comparisons will be performed using paired statistical tests (2-tailed paired *t* test or Wilcoxon signed rank test, depending on data distribution). Statistical significance will be set at *P*<.05.

**Results:**

Participant recruitment began in July 2026. At the time of submission of this revised manuscript, 3 participants had been enrolled. Recruitment and follow-up are ongoing. Data collection is expected to continue through late 2027, and the primary study results are expected to be available in early 2028, following completion of data collection and statistical analysis.

**Conclusions:**

This study will describe changes in clinical and patient-reported outcomes following multidisciplinary cancer pain committee assessment in routine clinical practice. Although causal inference is not possible because of the observational pre-post design, the findings may inform future optimization and evaluation of multidisciplinary cancer pain management pathways.

**Trial Registration:**

OSF Registries ty5m9; https://osf.io/ty5m9

**International Registered Report Identifier (IRRID):**

PRR1-10.2196/92566

## Introduction

### Background

Cancer-related pain is one of the most prevalent and debilitating symptoms in patients diagnosed with cancer and is likely the factor that most significantly affects and limits their quality of life [1]. The number of patients diagnosed with cancer continues to increase, as does cancer survival, largely owing to advances in diagnostic capabilities and oncological treatments; these improvements have contributed to increasing survival rates and, consequently, longer life expectancy after diagnosis [2]. As a consequence, this increased survival is associated with a higher burden of long-term adverse effects related both to the oncological disease itself and to its treatments, as well as with a growing number of patients experiencing cancer-related pain [3]. It is estimated that more than 50% of patients with cancer will experience pain at some point during the course of the disease [4], with this figure rising to 70% to 90% among patients with advanced disease, significantly affecting their physical, emotional, and social well-being.

According to the study by Sung et al [5], based on data analyzing 36 types of cancer across 185 countries, an estimated 19.3 million new cancer cases and 10 million cancer-related deaths occur worldwide each year. The most commonly diagnosed cancers were breast (11.7%), lung (11.4%), colorectal (10.0%), prostate (7.3%), and stomach cancer (5.6%). The cancers with the highest mortality were lung cancer (18.0% of all cancer deaths), colorectal cancer (9.4%), liver cancer (8.3%), stomach cancer (7.7%), and breast cancer (6.9%) [5]. Similar epidemiological trends have been reported in Spain according to data from the Spanish Network of Cancer Registries (REDECAN) [6]. With regard to metastases, although distribution depends on the type of primary tumor, the most common metastatic sites in descending order are lymph nodes, lungs, bones, and liver [7]. Bone is the third most common site of metastatic spread, particularly involving the axial skeleton (spine and pelvis) [8]. Bone metastases warrant special consideration due to their associated complications, especially pathological fractures and pain, which substantially compromise patients’ quality of life [9].

Cancer-related pain is usually somatic or mixed in nature and is less frequently purely neuropathic, although the type of pain depends on the characteristics of the oncological process. In addition to the tumor itself, oncological treatments such as chemotherapy, radiotherapy, and surgery may also be significant sources of pain. In the most recent revision of the World Health Organization’s (WHO’s) 11th revision of the International Classification of Diseases [10], cancer pain is defined either as chronic pain caused by the primary cancer or by metastases (chronic cancer pain), or as chronic pain resulting from cancer treatment, referred to as chronic postcancer treatment pain [11]. Several international organizations have developed clinical guidelines for the management of cancer-related pain, aiming to support optimal care, particularly in patients with advanced disease. In addition to the WHO analgesic framework, guidelines from the American Society of Clinical Oncology (ASCO) [12], the European Society for Medical Oncology (ESMO) [13], and the National Comprehensive Cancer Network (NCCN) [14] recommend individualized, multidisciplinary management, especially for patients with persistent, refractory, or complex pain requiring specialized interventions. These guidelines emphasize close collaboration among oncology, pain medicine, palliative care, rehabilitation, nursing, and psychosocial support services to optimize symptom control and deliver patient-centered care.

In general, most patients benefit from a multimodal approach that combines pharmacological treatment, interventional procedures, and physical and psychological therapies [3,15]. Pharmacological management has traditionally been based on the WHO analgesic ladder [16], which proposes a stepwise approach using nonopioid analgesics, weak opioids, and strong opioids, together with adjuvant medications according to the underlying pain mechanism (nociceptive, neuropathic, or mixed). However, this strategy has important limitations, particularly in patients with refractory pain, intolerance to opioid-related adverse effects, or localized pain that is difficult to control with systemic therapy [17]. Consequently, despite treatment with strong opioids and adjuvant medications, a substantial proportion of patients continue to experience uncontrolled pain or treatment-limiting toxicity [18]. In this setting, minimally invasive interventional procedures have become established as valuable adjuncts, especially in advanced or palliative disease. Available techniques, including nerve blocks, local anesthetic and corticosteroid injections, neuromodulation, and more recently ablative procedures, are selected according to the pain mechanism and underlying oncological condition to provide individualized pain relief whenever appropriate [19]. As cancer-related pain is frequently multifactorial and evolves throughout the disease trajectory, optimal management often requires coordinated multidisciplinary care. Accordingly, several models have been implemented in oncology practice, including specialized cancer pain clinics, palliative care consultation teams, integrated supportive care services, and multidisciplinary case conferences. Although their organizational structures differ, these models share the common goal of providing comprehensive assessment, facilitating shared clinical decision-making, optimizing pain management, and ensuring timely access to supportive and interventional therapies [20-24]. However, the scientific evidence supporting these organizational models remains limited. Most published studies have been retrospective observational studies or service evaluations performed in single institutions, with considerable heterogeneity in team composition, referral pathways, outcome measures, and follow-up. Consequently, the implementation and clinical outcomes associated with multidisciplinary cancer pain committees in routine clinical practice remain insufficiently characterized, highlighting the need for prospective observational studies evaluating patient outcomes after multidisciplinary assessment [25-28].

This study has therefore been designed as a prospective observational service evaluation protocol to characterize clinical outcomes, patient-reported outcomes, patient experience, and therapeutic decisions following multidisciplinary committee assessment. The multidisciplinary cancer pain management committee evaluated in this study is an established component of routine clinical care at our institution and was not created specifically for research purposes. The findings may enhance understanding of multidisciplinary cancer pain pathways and help inform future quality-improvement initiatives.

### Objectives

#### Primary Objective

The primary objective is to describe changes in pain intensity between baseline and 60 days following multidisciplinary committee assessment among patients with cancer-related pain managed in routine clinical practice.

#### Secondary Objectives

The secondary objectives are to assess patient-reported experience measures (PREMs) and patient-reported outcome measures (PROMs) [29] following multidisciplinary committee evaluation, to describe changes in opioid consumption measured as daily morphine equivalent dose (DMED), to characterize changes in treatment-related adverse effects associated with analgesic therapy, and to describe the therapeutic interventions proposed by the multidisciplinary committee.

Given the ethical and organizational nature of multidisciplinary cancer pain committees, randomization or withholding committee evaluation would not be feasible or ethically appropriate. A prospective pre-post design allows evaluation of clinically meaningful changes in pain and patient-reported outcomes while preserving routine clinical care. Although causal inferences cannot be made, this design is appropriate for evaluating the implementation of a multidisciplinary cancer pain management pathway in routine clinical practice.

## Methods

### Study Design and Setting

This is a prospective, observational, longitudinal pre-post study conducted at the Vigo University Hospital Complex, a tertiary care university hospital in Galicia, Spain.

### Study Timeline

Recruitment began in July 2026 and is expected to continue for approximately 18 months. At the time of submission of this revised manuscript, 3 participants had been enrolled. Final follow-up assessments are anticipated by late 2027, after which data analysis will be performed. Dissemination of the study findings through publication in a peer-reviewed journal is expected in early 2028.

### Study Population

The study comprises adult patients (aged ≥18 years) with histologically confirmed active cancer, defined as malignant disease requiring active antineoplastic treatment or with documented disease progression, who present with moderate to severe cancer-related pain (visual analog scale [VAS] ≥4) and are referred to the multidisciplinary cancer pain management committee. A VAS threshold of ≥4 was selected based on commonly accepted definitions of moderate pain intensity in oncology populations and its clinical relevance as an indication for treatment escalation [30].

### Study Procedures

#### Overview

The multidisciplinary cancer pain management committee constitutes part of routine clinical care and does not represent an experimental intervention. Participation in the study does not modify clinical decision-making or patient management. The study procedures comprise the following sequential steps as mentioned below.

#### Referral to the Multidisciplinary Committee

Patients are referred to the multidisciplinary cancer pain management committee by the treating physician whenever multidisciplinary assessment is considered clinically appropriate.

#### Multidisciplinary Committee Meeting

The committee meets monthly as part of routine institutional clinical practice. During each meeting, the referring physician presents the clinical case. Committee members review the patient’s oncological diagnosis, disease stage, ongoing cancer treatment, pain characteristics, previous analgesic management, imaging findings when available, and overall clinical status. Recommendations are established by multidisciplinary consensus after discussion of each case by all participating specialists. When different management options are considered appropriate, the final recommendation is reached through multidisciplinary agreement and documented in the patient’s clinical record.

#### Recruitment and Informed Consent

Patients meeting the eligibility criteria are invited to participate by the principal investigator during the first face-to-face visit to the pain unit following committee discussion. Written informed consent is obtained before study-specific data collection.

#### Baseline Assessment (T0)

Demographic characteristics, cancer-related variables, pain intensity, opioid consumption, quality of life, pain interference, adverse effects, committee recommendations, and their planned implementation are recorded.

#### Follow-Up

Patients continue receiving routine clinical care. Clinical follow-up is performed according to usual practice by the pain unit, either in person or by telephone depending on clinical needs. During follow-up, pain intensity, opioid treatment, adverse effects, implementation of committee recommendations, and clinically relevant events are documented.

#### Final Assessment (T1)

Sixty days after baseline, patients undergo the predefined outcome assessment, including pain intensity, quality of life, pain interference, opioid consumption, adverse effects, and PREMs.

The primary analysis will compare baseline (T0) and 60-day (T1) assessments (Table 1). Information collected during routine follow-up will primarily be used for clinical monitoring and descriptive analyses.

**Table 1 table1:** Schedule of assessments and data collection time points.

Variable	Baseline (T0)	Routine clinical follow-up	60 days (T1)
Informed consent	✓		
Demographics	✓		
Cancer characteristics	✓		
VAS^a^	✓	✓	✓
EQ-5D	✓		✓
BPI-SF^b^	✓		✓
DMED^c^	✓	✓	✓
Adverse effects	✓	✓	✓
PREMs^d^ (satisfaction)			✓
Committee recommendations	✓		
Implementation of recommendations		✓	✓

^a^VAS: visual analog scale.

^b^BPI-SF: Brief Pain Inventory–Short Form.

^c^DMED: daily morphine equivalent dose.

^d^PREM: patient-reported experience measure.

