### Study Outcomes

The primary outcome is the change in pain intensity, measured using the VAS, from baseline (T0) to 60 days (T1) following multidisciplinary committee assessment. A reduction of at least 1 point on the VAS was predefined as the minimal clinically important difference, based on previous literature in patients with cancer-related pain [31]. This threshold was used for the sample size calculation and will also serve to interpret the clinical relevance of the observed changes.

Secondary outcomes include changes between T0 and T1 in health-related quality of life measured using the EQ-5D [32], pain-related functional interference assessed with the Brief Pain Inventory–Short Form (BPI-SF) [33], DMED, analgesic treatment–related adverse effects, and PREMs, including satisfaction with care assessed using a Likert-scale questionnaire at T1.

Table 2 summarizes the study outcomes, instruments, and time points. The primary analysis will focus on paired comparison of VAS scores between T0 and T1. Secondary outcomes listed in Table 2 will be analyzed accordingly based on variable type and distribution.

**Table 2 table2:** Study outcomes.

Outcome category	Variable	Instrument or source	Time points	Type
Pain intensity	VAS^a^ score (0-10)	VAS	T0 and T1	Primary
Quality of life	EQ-5D index score	EQ-5D questionnaire	T0 and T1	Secondary
Pain interference	BPI-SF^b^ interference score	BPI-SF	T0 and T1	Secondary
Opioid consumption	Daily morphine equivalent dose (mg/day)	Clinical record	T0 and T1	Secondary
Adverse effects	Presence or absence and type	Clinical assessment	T0 and T1	Secondary
Committee recommendation	Type of recommendation issued	Committee record	T0	Descriptive
Implementation of recommendations	Implementation status (implemented, partially implemented, or not implemented)	Electronic medical record	T1	Exploratory
Patient satisfaction	Likert-scale satisfaction score	PREM^c^ questionnaire	T1	Secondary

^a^VAS: visual analog scale.

^b^BPI-SF: Brief Pain Inventory–Short Form.

^c^PREM: patient-reported experience measure.

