Because of the observational design, the relatively small sample size, and the exploratory nature of these analyses, adjusted regression models will be considered hypothesis-generating and interpreted with appropriate caution. Predefined exploratory subgroup analyses will be performed whenever sample size permits. These analyses may include comparisons according to cancer type, metastatic vs nonmetastatic disease, baseline pain severity (moderate vs severe), and patients who are receiving palliative vs nonpalliative care. These subgroup analyses will be considered exploratory and interpreted cautiously.

Analyses will primarily be conducted using complete-case analysis. The frequency, pattern, and potential reasons for missing data will be described. In patients with advanced cancer, missing outcome data may result from clinical deterioration, hospitalization, or death and may therefore be informative (missing not at random). If missing data for the primary outcome exceed 5%, multiple imputation will be considered only as part of sensitivity analyses and only if the missing-data mechanism is considered reasonably compatible with the missing-at-random assumption. The results of any imputation-based analyses will be interpreted cautiously in light of the potential for informative missingness. Additional sensitivity analyses, including complete-case analyses, will be performed whenever appropriate to assess the robustness of the primary findings. All analyses will follow the predefined statistical plan approved by the research ethics committee.

As this is an observational study protocol rather than a clinical trial, the manuscript was primarily prepared in accordance with the STROBE (Strengthening the Reporting of Observational Studies in Epidemiology) statement [34]. Elements of the SPIRIT (Standard Protocol Items: Recommendations for Interventional Trials) statement were considered where applicable to improve protocol transparency [35].

A participant flow diagram will be used to describe progression through the study, including numbers assessed for eligibility, enrolled, completing follow-up, and included in the final analysis.

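### The main pain-change estimate is a complete-case T0/T1 comparison that leaves out VAS scores recorded in between, so it may overstate the fall if loss follows deterioration

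*Protocol article*

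**What the plan says.** All references are to the Methods of the protocol article.

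- **What is recorded.** The Follow-Up section states: "During follow-up, pain intensity, opioid treatment, adverse effects, implementation of committee recommendations, and clinically relevant events are documented". Table 1 ticks VAS, DMED and adverse effects under routine clinical follow-up as well as at T0 and T1. No day is set for these contacts: "Clinical follow-up is performed according to usual practice by the pain unit, either in person or by telephone depending on clinical needs".
- **How follow-up data are to be used.** Final Assessment (T1): "Information collected during routine follow-up will primarily be used for clinical monitoring and descriptive analyses".
- **The primary comparison.** Study Outcomes: "The primary analysis will focus on paired comparison of VAS scores between T0 and T1". The Statistical Analysis Plan section gives the test as a paired *t* or Wilcoxon signed rank test.
- **Missing day-60 scores.** The same section says: "Analyses will primarily be conducted using complete-case analysis". It also says of patients with advanced cancer that "missing outcome data may result from clinical deterioration, hospitalization, or death and may therefore be informative (missing not at random".
- **Sensitivity analyses.** If more than 5% of the primary outcome is missing, "multiple imputation will be considered only as part of sensitivity analyses", and then only if missing at random is reasonable. The one other sensitivity analysis named is complete-case, which is the main analysis again.

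**The concern.** Take a patient with VAS 7 at T0 and VAS 9 at a telephone contact around day 30 who is then admitted and has no T1 assessment. The worsening was measured on the primary scale and entered in the study data, yet the patient is absent from the main estimate. The plan expects losses of this kind, and the recorded variable closest to the reason for loss is the one assigned to monitoring and description.

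If patients who are getting worse are the ones lost, those who remain show a larger mean fall than the enrolled group had. This bears on interpretation because Study Outcomes uses a 1-point reduction as the yardstick for clinical relevance, so a modest bias could carry a true fall below 1 over that line. The fallback does not clearly help. Multiple imputation is conditional, its predictors are not named, and repeating the complete-case analysis cannot reveal a bias that it shares.

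**Working it through.** **1. The plan's own loss figure.** Sample Size and Power Calculations allows 5% dropout: 64 / (1 − 0.05) = 67.4, rounded up to 68. This step reproduces. (How the 64 was reached is a separate matter.) The imputation trigger is more than 5% missing, and 5% of 68 is 3.4. Three missing patients (4.4%) would not trigger it; four (5.9%) would.

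**2. Exact form of the bias.** With a fraction *p* lost,

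bias = *p* × (mean fall in completers − mean fall in those lost).

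The second factor is unknown, so a range is shown:

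| Lost | Lost improve 1 point more | No difference | 1 less | 2 less | 3 less |
|---|---|---|---|---|---|
| 5% | −0.05 | 0 | 0.05 | 0.10 | 0.15 |
| 20% | −0.20 | 0 | 0.20 | 0.40 | 0.60 |
| 30% | −0.30 | 0 | 0.30 | 0.60 | 0.90 |

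**3. Simulation: can the interim VAS help?** From the plan: SD 2, and a true mean fall set at its 1-point threshold. Assumed: one interim VAS near day 30; correlations T0/interim 0.4, T0/T1 0.3, interim/T1 0.7; probability of loss logistic with slope 0.3 to 1.0 per VAS point. Three estimates of the mean fall (true value 1.00) are compared: complete cases; T1 predicted from T0 alone; T1 predicted from T0 and the interim VAS. Independent runs agree to about 0.02.

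| Loss depends on | Lost | Complete-case | With interim VAS |
|---|---|---|---|
| Change from T0 to interim | 5% | 1.06–1.15 | 1.00 |
| Change from T0 to interim | 20% | 1.23–1.50 | 1.00 |
| Interim level | 5% | 1.02–1.05 | 1.00 |
| Interim level | 20% | 1.07–1.16 | 1.00 |
| Change from T0 to T1 (not at random) | 20% | 1.31–1.66 | 1.12–1.29 |
| T1 level (not at random) | 20% | 1.16–1.36 | 1.12–1.31 |

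The first four rows give the overstatement when loss follows the interim VAS: 0.02 to 0.15 at 5% and 0.07 to 0.50 at 20%. In those rows loss is missing at random by construction, so full recovery is built in. In the last two rows recovery is partial at best.

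A second run used correlations 0.5/0.5/0.7 and slope 0.5, at 20% loss. Loss unrelated to pain gave 1.00 on complete cases. Loss of good responders gave 0.93 (1.00 with interim VAS). Loss driven by the T1 level gave 1.17 on complete cases and 1.18 with interim VAS, so no repair.

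**4. Which predictors enter the imputation.** When loss follows the interim level at 20%, predicting T1 from T0 alone gives 1.14 to 1.32, further from 1.00 than complete-case (1.07 to 1.16). This does not hold when loss follows the interim change. Imputation without the interim VAS can therefore make matters worse.

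**5. Partial coverage.** If only 60% of patients have an interim value and loss follows the interim change, the estimate using it is 1.03 to 1.18 for losses of 10% to 30%.

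**6. Scale.** Reading SD 2 as the SD of the change, the standard error with 64 patients is 2/√64 = 0.25. A bias of 0.02 to 0.15 is under one standard error. With 54 completers (20% of 68 lost) it is 2/√54 = 0.27, and 0.07 to 0.50 is roughly 0.3 to 1.8 standard errors.

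**The case against.** The strongest reply has four parts.

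*The planned loss is small.* Dropout is put at 5%, and Exclusion Criteria removes patients whose expected survival is too short for follow-up. At 5% the bias in these scenarios is at most about 0.15. This stands. The larger figures need several times the planned loss.

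*The wording is not absolute.* Final Assessment (T1) says *primarily*, conditional imputation could bring lost patients back, and nothing bars the interim VAS as a predictor. This also stands. A reader might infer that follow-up VAS is shut out of every pain analysis; the documents support this only for the main estimate. It is the complete-case rule that drops the patients, more than the sentence on follow-up data.

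*Unscheduled scores make poor primary data.* Resting the primary endpoint on two fixed assessments is defensible. A reader might take Table 1 to promise every patient an interim VAS, but its column names routine follow-up without a day, and a patient who declines quickly may have none. In addition, a mixed model over all enrolled patients would extrapolate pain scores beyond death. These points limit the remedy to a companion analysis.

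*Imputation predictors belong in the full analysis plan, which is not shown.* This is true of the predictor list alone, and its absence is not the point here. The article does state a use for follow-up data, a complete-case main analysis and a sensitivity analysis that repeats it. Those are stated choices and can be judged as such.

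**Conclusion.** The point holds in a limited form. The main estimate ignores post-baseline values of the primary variable, while the plan expects informative loss and names no sensitivity analysis certain to use them. If loss follows deterioration, the mean fall may be overstated: by about 0.02 to 0.15 points at 5% loss and 0.07 to 0.50 at 20%, when loss follows the interim VAS. These sizes rest on assumed correlations, slopes and a single interim score; none comes from the documents.

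A reader might go further and conclude that the reported fall *will* be overstated. The documents do not support that. They say only that missing data may be informative and give neither direction nor size. The bias is zero if loss is unrelated to pain and reversed if good responders leave. Nor would the interim VAS cure the problem: under loss not at random, the mechanism the plan itself raises, it repairs the estimate in part or not at all. At the planned loss this is a modest, inexpensive improvement; it becomes important if loss runs well above 5%.

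**What to change.** 1. Keep the paired T0/T1 test as primary.
2. In Final Assessment (T1), state that VAS recorded at routine follow-up may also be used in sensitivity analyses of the primary outcome.
3. In the Statistical Analysis Plan section, replace the repeated complete-case sensitivity analysis with one of two: a likelihood-based repeated-measures model on all recorded VAS values with contact date, or multiple imputation using those values and dates plus follow-up DMED and adverse effects as predictors. Either estimates the T0-to-day-60 change.
4. Report beside it a delta-adjusted analysis in which unobserved day-60 scores are made progressively worse than predicted, over a range fixed in advance.
5. Report deaths before day 60 separately and do not impute pain after death. State how many patients without T1 had an interim VAS.

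The cost is a few lines of text, one or two further models, and a dated update to the preregistration and the ethics-approved plan. No new assessments are needed, and with 3 participants enrolled at submission the choice can still be made before results are known. The limits should be stated with the results: contacts are unscheduled and driven by need, some lost patients will have no interim value, and loss not at random is only partly addressed.
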